### Sample Size

The sample size cannot be formally calculated because it depends on the incremental improvement in the accuracy of Lifelight achieved through machine learning using the training data generated in the study. However, indicative sample sizes for the 4 subprotocols have been calculated by assessing the optimal data requirements to enable algorithm training toward the standards defined in Table 3, balanced against the practicality of achieving the targets. The split between training and testing data will be determined during the study according to the quality of the data collected.

The initial protocol anticipated data collection from about 8400 participants for training and a further 1000 for independent testing of accuracy, but the recruitment has been compromised by restrictions implemented during the COVID-19 pandemic. However, the high-quality video recording (compared with VISION-D and VISION-V) supported a protocol amendment to reduce the recruitment to 1950 participants (see Results section), with the expectation that data from about 1700 will be used for training the algorithms and data from 250 used for testing. The study management team is monitoring the progress of data collection and accuracy, and updates the study teams monthly. The study will continue until the accuracy of Lifelight for measuring VS is sufficient for various clinical use cases.

As skin tone is expected to affect the accuracy of Lifelight, the aim is to recruit participants across the full Fitzpatrick skin tone scale (1-6). To allow the impact of skin tone measurement accuracy to be determined with statistical robustness, the full data set will be sampled to create a subset for skin tone analyses in which the prevalence of the usually less prevalent skin tones is amplified. This subset will contain 750-1000 measurements, with 15%-20% each from categories 1, 2 and 3, 4, and 5 and 6. These measurements should be spread across the subprotocols as indicated in Table 3.

**Table 3 table3:** Indicative sample size targets.

Subprotocol	Indicative sample size, n^a^	Characteristics	Participants with skin tone categories 1, 4, 5, and 6
1	1500	Roughly 100 participants will be recruited with SOC^b^-determined SBP^c^ in each 10 mm Hg increment from <90 mm Hg to >200 mm Hg (ie, <90 mm Hg; 90-99 mm Hg; 100-109 mm Hg, etc)^d^	Ideally ≥4 in each SBP band
2	375	N/A^e^	Ideally ≥10 in each SBP band
3	35	Approximately 33% with SOC-measured oxygen saturation <88%, 88%-92%, and 93%-95%	Ideally, each band will include participants with each skin tone
4	No specific target; likely to be a small proportion	N/A	N/A

^a^Participants in subprotocol 4 (ie, those without the capacity to provide informed consent) are likely to have vital sign values outside of the normal range and will contribute to all subprotocol targets. Only the first study session per participant contributes to the sample size.

^b^SOC: standard of care.

^c^SBP: systolic blood pressure.

^d^Can include participants with SBP measured from an arterial line.

^e^N/A: not applicable.

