**Results:**

Recruitment began in May 2021 but was hindered by the restrictions instigated during the COVID-19 pandemic. The development of data processing methodology is in progress. The data for analysis will become available from September 2022, and the algorithms will be refined continuously to improve clinical accuracy. The performance of Lifelight compared with that of the standard-of-care measurement of VS will then be tested. Recruitment will resume if further data are required. The analyses are expected to be completed in early 2023.

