Recruitment started in May 2021 but was compromised by restrictions implemented during the COVID-19 pandemic to limit access to hospitals by the general public. Protocol amendments were made to increase community recruitment in light of these issues. Target recruitment is approximately 1950 participants to generate measurements for use in the initial training data set and for performance testing. However, the final sample size will depend on the incremental improvement in accuracy of the Lifelight algorithm and therefore cannot be predicted (see Sample Size section). The study will continue until the accuracy of Lifelight for measuring VS is sufficient for various clinical use cases.

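### The continue-until-sufficient rule does not separate training accuracy from the held-out test, so it permits repeated testing until a pass

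*Protocol article*

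**What the plan says.** Stopping. The Sample Size section says "The study will continue until the accuracy of Lifelight for measuring VS is sufficient for various clinical use cases", and the same sentence appears under Participants and Recruitment. That section also says "However, the final sample size will depend on the incremental improvement in accuracy of the Lifelight algorithm and therefore cannot be predicted". Neither place links sufficient accuracy to Table 2, limits the number of rounds, or says what happens if the targets are missed.

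Sequence. The Results paragraph of the abstract describes continuous refinement of the algorithms and then says "The performance of Lifelight compared with that of the standard-of-care measurement of VS will then be tested". The next sentence is "Recruitment will resume if further data are required".

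Split and monitoring. The Sample Size section says "The split between training and testing data will be determined during the study according to the quality of the data collected", although it also gives expected numbers: "with the expectation that data from about 1700 will be used for training the algorithms and data from 250 used for testing". On oversight it says "The study management team is monitoring the progress of data collection and accuracy, and updates the study teams monthly", without saying on which data accuracy is monitored.

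Separation. The abstract (Methods) and the Discussion say that data are retained for testing. The Introduction assigns initial data to machine learning and later data to testing. Data Analysis places the test against Table 2 after training.

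**The concern.** Collecting training data until an algorithm is good enough is normal in development work, and development is the primary objective here. The difficulty is that one open-ended rule covers the whole study, including the test against predefined targets. If a missed target can lead to more recruitment, more refinement and another test, while a met target ends the study, the reported test result has been selected because it passed. Each further test is another chance to pass by luck, and reuse of the same held-out participants also tunes the algorithm to them. What is at stake is the meaning of a statement that Lifelight meets its Table 2 targets: its false-pass rate would depend on an unstated number of attempts.

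**Working it through.** **The plan's own figures.** 1700 + 250 = 1950, as stated. The Table 3 targets sum to 1500 + 375 + 35 = 1910. No alpha or power is stated, so there is no power calculation to reproduce.

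**Inputs.**
- Target: systolic error SD ≤ 8 mm Hg (Table 2), treated as a point rule because no confidence bound is given.
- Test set: 250 participants. Blood pressure is measured only in subprotocols 1 and 4 (Table 1), and subprotocol 4 has no numerical target. Pro rata, 250 × 1500/1910 ≈ 196. This is an assumption; the make-up of the test set is not given.
- Assumed: normal errors, one reading per participant, true accuracy unchanged between tests, true SD 8.25, 8.5 or 9.0, and five tests.

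**One test.** P(pass) = P(χ² with n − 1 df ≤ (n − 1) × 8²/σ²), with n = 196:
- σ = 8.25: 195 × 64/68.06 = 183.4, giving 0.285
- σ = 8.5: 195 × 64/72.25 = 172.7, giving 0.127
- σ = 9.0: 195 × 64/81 = 154.1, giving 0.014

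**Five tests, three ways.**
- Fresh test sets: 1 − (1 − p)⁵. For σ = 8.5, 1 − 0.873⁵ = 0.49.
- Five algorithm versions on one reused set, by simulation, with errors of different versions correlated 0.9 to 0.5.
- New test data pooled with the old at each look, by simulation.

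| True SD | One test | Five fresh sets | Five versions, same set | Five cumulative looks |
|---|---|---|---|---|
| 8.25 | 29% | 81% | about 47–71% | about 39% |
| 8.5 | 13% | 49% | about 25–42% | about 15% |
| 9.0 | 1.4% | 7% | about 4–6% | about 1% |

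**Sensitivity to n.** If all 250 contributed blood pressure, one test at σ = 8.5 would pass 9.8% of the time, and five fresh sets would give at least one pass 40% of the time.

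**Sensitivity to repeat readings.** Table 1 gives three measurements in subprotocol 1. With three readings per participant and an assumed intraclass correlation of 0.3 to 0.7, one test at σ = 8.5 passes about 3–8% of the time. By the same formula, five fresh sets give 1 − 0.97⁵ = 14% to 1 − 0.92⁵ = 34%. The absolute figures fall, but retesting still raises them several-fold.

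**The case against.** A reader might infer that the plan is to retest Lifelight until it passes, or that the study can only end in success. The documents do not support either statement. No sentence mentions a retest. The words "Recruitment will resume if further data are required" give no trigger: further data may mean more training data, or systolic bands left unfilled after pandemic-limited recruitment. The Sample Size section ties the sample size to learning from training data. Monthly accuracy monitoring may likewise be confined to training data. The article keeps test data apart in several places, gives a target of about 1950, and expects final analyses against Table 2 in early 2023. Version locking and single use of a test set are also details that a condensed article may leave to a fuller document.

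All of this stands against the stronger reading. It does not remove the point. Retaining data and testing after training do not say that the test happens once. The target of 1950 is not a cap, because the final number is said to be unpredictable. The split itself can move while accuracy is being watched. The problem is also not only silence: the article states a stopping rule, and safeguards in another document would have to override it.

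On size, the objection has force. A true SD of 8.5 is a near miss, and the inflation at 9.0 is small. Cumulative pooling adds little. Accuracy would probably change with retraining, so some later passes would be real improvement. Only the systolic SD was modelled; Table 2 also requires British Hypertension Society Grade C and has targets for pulse rate, respiratory rate and oxygen saturation.

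**Conclusion.** The point holds as a matter of what the stated rule permits. As written, the result of the held-out test may decide whether it is the last one, and a device that narrowly misses a target could then be reported as meeting it. Whether this is intended cannot be told from the article.

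For a near miss the effect can be large: from 29% to between 39% and 81% at true SD 8.25, and from 13% to between 15% and 49% at 8.5, over five tests. For a clear failure at 9.0 it stays at 7% or less. These figures rest on the assumed 196 participants, normal errors, one reading each, five attempts and constant true accuracy. They illustrate the risk and do not predict this study's outcome.

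**What to change.** Amend the protocol wording before any held-out accuracy is seen:

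1. State that the continue-until-sufficient rule, the monthly accuracy monitoring and any decision to resume recruitment use cross-validated accuracy in training participants only.
2. Fix which participants are held out before their accuracy is seen, in place of a split decided as the study goes along.
3. Open the held-out set once, on a version-locked algorithm, and report the result against Table 2 whether it passes or fails.
4. If development continues after that, the opened set may join training. Any later claim uses newly recruited held-out participants, and the number of attempts is reported.

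The first three steps are wording only and leave iterative development on training data untouched. The cost is that a failed first test must be reported and a later claim needs a new test set.

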**Methods:**

The study is recruiting adults (aged ≥16 years) who are inpatients (some critically ill), outpatients, and healthy volunteers, aiming to cover a broad range of normal and clinically relevant VS values; there are no exclusion criteria. High-resolution 60-second videos of the face are recorded by the Lifelight app while simultaneously measuring VS using standard-of-care methods (automated sphygmomanometer for blood pressure; finger clip sensor for pulse rate and oxygen saturation; manual counting of respiratory rate). Feedback from patients and nurses who use Lifelight is collected via a questionnaire. Data to estimate the cost-effectiveness of Lifelight compared with standard-of-care VS measurement are also being collected. A new method for rPPG signal processing is currently being developed, based on the identification of small areas of high-quality signals in each individual. Anticipated recruitment is 1950 participants, with the expectation that data from approximately 1700 will be used for software development. Data from 250 participants will be retained to test the performance of Lifelight against predefined performance targets.

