#### VS measurement

The study staff ensure that participants have been at rest for at least 10 minutes before VS measurement starts and that they have not consumed any food or drink in the previous 30 minutes (other than intravenous fluids or nasogastric feeding). In each study session, VS is measured as per the subprotocol using the standard-of-care equipment while simultaneously capturing a video of the participant’s face using the Data Collect app running on a tablet (standard iPad 9.7, 2018) positioned approximately 1 m away and angled toward the participant’s face. Controls and instructions on the device start and stop the 60-second video recording. Background luminosity is measured using a handheld lux meter. The study staff have been briefed on the optimum Lifelight measurement conditions. Recordings are repeated once or twice, as set out in Table 1. The app does not return any measurements to the user or participant.

VS measurements are taken and coordinated by 2 nurses, one of whom announces the start and finish of the recording period on the Data Collect app. BP is measured using a standard clinical automatic sphygmomanometer with an appropriately sized cuff (width at least two-thirds of upper arm length) on the participant’s nondominant upper arm (unless contraindicated) or via an arterial line if fitted. BP is recorded at the start of the recording period. A standard clinical finger clip sensor for the measurement of oxygen saturation and pulse rate is placed on a finger on the opposite side of the body to the sphygmomanometer. Oxygen saturation and pulse rate are measured at 0, 30, and 60 seconds of the recording period and averaged. Respiratory rate is determined manually by counting chest rises throughout the 60-second period. The nurse may place their hand on the participant’s chest to increase the accuracy of manual counting but being mindful not to obscure the camera’s line of sight.

Each study session takes approximately 30 minutes. Once the measurements are completed, the study staff complete the postmeasurement observation questions relating to how much the participant moved, their position, whether they were wearing glasses, any hairstyle or other item (eg, face covering) that obscured any part of their face during the recording, and whether the software reported “face not found” at any point during the recording.

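### The skin-tone accuracy subset is drawn from the full data set, most of which is expected to train the algorithm, so accuracy by skin tone would be largely in-sample

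*Protocol article*

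**What the plan says.** The Sample Size section states the purpose of the skin-tone analysis as "To allow the impact of skin tone measurement accuracy to be determined with statistical robustness". To that end "the full data set will be sampled to create a subset for skin tone analyses", in which the less common tones are over-represented. On size and mix: "This subset will contain 750-1000 measurements, with 15%-20% each from categories 1, 2 and 3, 4, and 5 and 6".

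The same section describes "a protocol amendment to reduce the recruitment to 1950 participants", with the expectation that "data from about 1700 will be used for training the algorithms and data from 250 used for testing". It adds that "The split between training and testing data will be determined during the study according to the quality of the data collected".

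The abstract gives the role of the held-out data: "Data from 250 participants will be retained to test the performance of Lifelight against predefined performance targets". The Data Analysis section likewise ties the test data to the Table 2 targets and does not mention skin tone. Nothing in the article limits the skin-tone subset to held-out participants or mentions cross-validated prediction.

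On recordings per session, the VS measurement section says: "Recordings are repeated once or twice, as set out in Table 1". Table 1 gives 3 measurements in subprotocols 1 and 4, and 2 in subprotocols 2 and 3.

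**The concern.** An algorithm scored on the participants it was fitted to tends to look more accurate than it will be in new patients. The plan accepts this for overall performance, since it keeps 250 participants back. For skin tone, a factor that the Sample Size section itself expects to affect accuracy, it names a data source made up mainly of training participants.

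Skin tone is one of the variables listed under secondary objective 2, and the primary objective also refers to patients with different skin tones. If the subset is largely in-sample, the error reported for each skin tone is likely to be too small. A real gap between tones may also be narrowed, because a flexible model can fit a small group closely during training. A finding of little or no skin-tone effect would then be weak evidence about new patients.

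**Working it through.** **Inputs.** Training about 1700, test 250, total 1950, subset 750-1000 measurements, share 15%-20% per group (Sample Size). Targets of 1500, 375 and 35 for subprotocols 1-3; subprotocol 4 has none (Table 3). Measurements per session of 3, 2 and 2 (Table 1). Up to 10 sessions per participant (Subprotocol assignment).

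**The plan's own figure.** 1700 + 250 = 1950, which reproduces the recruitment target. The Table 3 targets sum to 1500 + 375 + 35 = 1910, close to it. The article gives no alpha, power or effect size, so no power calculation applies.

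**Expected make-up of the subset.** Assume that sampling is unrelated to the split and that training and test participants contribute similar numbers of recordings.
- Training share: 1700/1950 = 87.2%. Held-out share: 250/1950 = 12.8%.
- Training measurements: 0.872 × 750 ≈ 654 to 0.872 × 1000 ≈ 872.
- Held-out measurements: 750 − 654 = 96 to 1000 − 872 = 128.
- One group: 0.15 × 750 = 112.5 to 0.20 × 1000 = 200 measurements. Held-out part: 112.5 × 0.128 ≈ 14 to 200 × 0.128 ≈ 26.

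**What the held-out participants can supply.**
- One session each: 250 × 2 = 500 to 250 × 3 = 750 measurements.
- Table 3 mix: (1500 × 3 + 375 × 2 + 35 × 2)/1910 = 5320/1910 = 2.79 per participant, so 250 × 5320/1910 ≈ 696.
- Number that must come from training participants even if every held-out first-session recording is used:

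| Subset size | 3 per participant | Table 3 mix | 2 per participant |
|---|---|---|---|
| 750 | 0 | 54 (7%) | 250 (33%) |
| 1000 | 250 (25%) | 304 (30%) | 500 (50%) |

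These are minima. Selecting for less common tones would raise them, and repeat sessions would lower them.

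**Direction of the bias (assumed inputs, illustration only).** Least-squares models were fitted to predictors carrying no signal, with 1500 common-tone participants (error SD 8) and 200 rare-tone participants (error SD 10), over 40 repetitions. RMSE is given as common / rare.

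| Predictors: shared + per group | In-sample | Gap | New participants | Gap |
|---|---|---|---|---|
| 20 + 0 | 7.95 / 9.81 | 1.86 | 8.04 / 10.11 | 2.07 |
| 100 + 0 | 7.79 / 9.62 | 1.83 | 8.28 / 10.16 | 1.88 |
| 300 + 0 | 7.30 / 8.84 | 1.54 | 8.87 / 10.70 | 1.83 |
| 50 + 25 | 7.84 / 9.18 | 1.34 | 8.16 / 10.86 | 2.70 |
| 100 + 50 | 7.65 / 8.33 | 0.68 | 8.43 / 11.76 | 3.33 |

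In-sample error is lower in both groups in every setting. The effect on the gap ranges from negligible to large. In the first two rows it is within simulation error: the rare-group RMSE alone has a standard error of about 10/√(2 × 200 × 40) = 0.08.

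**Shares.** Read as four groups (1; 2 and 3; 4; 5 and 6), 15%-20% each totals 4 × 15% = 60% to 4 × 20% = 80%. Read as six categories, it totals 6 × 15% = 90% to 6 × 20% = 120%.

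**The case against.** The strongest reply is that the text fixes which recordings are sampled, not which predictions are scored. The sentence sits under Sample Size, and a full protocol or SAP, not shown here, could require cross-validated predictions for training participants. That is possible, so in-sample scoring is an inference. It is still the natural one: the section speaks of training and testing data separately, then chooses the full data set, and the subset is to be spread over subprotocols as in Table 3, which describes whole-study recruitment.

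Second, the 87% is a scenario. The split is still to be decided and sampling could favour test participants. This stands, and the figure is given with its assumption.

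Third, the Table 2 performance claims are assigned to test data. This also stands: the point does not reach them.

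A reader might infer three stronger things that the article does not support:
- That the subset cannot come from held-out participants alone. Three recordings from each of 250 participants give 750, the lower limit. Up to 10 sessions are also allowed, and the first-session rule in the Table 3 footnote governs the sample-size count, not this subset.
- That over-representing rare tones by sampling achieves nothing. Recruitment by skin tone is allowed (Subprotocol assignment) and Table 3 sets desired minimum numbers, so rare-tone participants can be added.
- That the shares are wrong. The punctuation is ambiguous, the six-category reading includes 100%, and the text does not say that four groups must fill the subset.

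**Conclusion.** The point holds. Following the stated rule gives a mostly in-sample answer to part of secondary objective 2: about 87% training data, with about 14-26 held-out measurements per group, if sampling is unrelated to a split near 1700/250. Held-out data may fall short of the stated subset size (about 696 against 750-1000 at the Table 3 mix) unless repeat sessions are used.

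Error in new patients is likely to be understated, and differences between tones may be. It would go too far to say that the tones will look equal. That depends on a model the article does not describe, and the illustration ran from almost no change in the gap to a large one. The share wording is a query to clear up, secondary to the main point.

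**What to change.** In the Sample Size section, replace sampling from the full data set with a rule that skin-tone accuracy is computed only from predictions by a model that never saw that participant. That means the held-out participants and, if more numbers are needed, out-of-fold predictions for training participants, with all recordings and sessions of a participant kept in the same fold. Report bias and SD or RMSE by Fitzpatrick group. State whether the 15%-20% shares refer to four groups or six categories and, if four, what makes up the rest of the subset.

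The cost is a change of wording and some computing time for cross-validation. No extra participants are needed. The reported skin-tone errors may be less favourable. The split is still open, so the change can be made within the plan as it stands.
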